**Figure 1 Fig1:**
[figure not shown]
**Flow chart of participants through study.**

### Eligibility criteria

Female volunteers will be eligible for participation in the trial on the basis of the following criteria: age 18 to 40 years, insidious onset of pain unrelated to any traumatic event, pain located between the knee and ankle of at least one month duration that is aggravated by weight bearing activities such as running, hopping or jumping, and worst pain over the previous week of at least 30 mm on a 100 mm visual analogue scale. Volunteers will be excluded from the trial in the presence of any of the following: a history of surgery to the lower limb, a cardiac condition, a known allergy to adhesive strapping tape, or symptoms of radiculopathy or other neurological involvement. Extensive previous exposure to either taping technique will also exclude volunteers from participation in order to prevent bias to one intervention.

### Recruitment of participants

Female volunteers will be recruited from paid advertisements in local community newspapers, supplemented by regular postings of advertisements on noticeboards within the University and wider community (e.g. gymnasiums, sporting clubs, health clinics). Each potential participant who responds to advertisements will undergo a screening process (via phone or email) to determine eligibility. Eligible volunteers will be provided with an information sheet thoroughly explaining the study and informed written consent to participate in the study will be obtained. Once eligibility has been determined and the informed consent process completed, participants will be assigned an identification number. Enrolled participants will attend a baseline testing session at which an assessor blinded to group allocation will obtain demographic information (age, weight, height), clinical characteristics of ERLP (nature, location, duration, onset, previous treatment), exercise history (intensity, duration and modality of current participation, and participation prior to the onset of ERLP), and perform outcome measurements. At the conclusion of baseline outcome measurements, the participant will be notified of group allocation by the treating physiotherapist and the intervention will commence.

### Randomisation

For group allocation, a computer-generated table of random numbers (in three blocks) will be used for the randomisation sequence. An individual not otherwise involved in the study will place the randomisation sequence in a series of consecutively numbered opaque envelopes, and sign across the seal of the envelope. Allocation will be concealed from the outcome assessor for the duration of the trial.

### Intervention

The interventions will be performed by one of two registered physiotherapists (Physiotherapy Board of Australia), each with at least 10 years of experience in musculoskeletal physiotherapy. In addition, both physiotherapists will have completed two comprehensive training sessions together for explanation and discussion of the standardised intervention protocol for the trial. A detailed written protocol outlining trial procedures will be provided to treating physiotherapists. This will include standardised instructions for participant advice, application of both the rigid and elastic taping techniques, prescription of the lower limb muscle training exercises, and recording of treatment. Over a six week intervention period participants will receive one of three treatments: (i) lower limb muscle training alone, (ii) combined intervention of rigid tape and lower limb muscle training, (iii) combined intervention of elastic tape and lower limb muscle training.

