### Study design

A randomised controlled clinical trial will be conducted in a community setting over a 12 month period. The Australian Catholic University Human Research Ethics Committee has granted ethical approval and all participants will provide informed written consent prior to commencement in the trial. An individual independent to the trial will perform the computer-generated randomisation sequence and preparation of envelopes containing the group allocation. The physiotherapist will communicate with participants regarding group allocation; due to the nature of the intervention it will not be possible to blind the treating physiotherapist or the participants. An assessor blinded to group allocation will perform outcome measurements at all time points. Data entry and statistical analysis will be performed by a blinded assessor. Figure 1 provides an overview of the study protocol.

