### Planned statistical analysis

Data processing, data entry and data analysis will be performed by an assessor who is blinded to group allocation. The primary analysis of the data will be performed on an intention-to-treat basis. SPSS software (version 21.0) will be used for statistical procedures. Demographic data, clinical characteristics of pain and physical activity level at baseline will be examined for comparability across the three intervention groups. To evaluate the effect of the interventions on pain and function (VAS, FAAM, PSFS, Physical activity level) a two-way repeated measure analysis of variance with between subject factor of intervention group and within subject factor of test session, will be performed. Global perceived effect will be dichotomised to either success (completely recovered, much improved, improved) or no success (no change, worse, much worse) and expressed as relative risk reduction and numbers needed to treat. For all statistical procedures age, weight and height will be included as covariates and alpha level will be set at 0.05.

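### Two unblinded physiotherapists deliver the treatment, but neither the stated randomisation nor the fixed covariate list allows for which one; the cost is chance imbalance and some lost precision, not systematic bias

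*Protocol article*

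**What the plan says.** All statements are from the protocol article.

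- **Who treats (Intervention):** "The interventions will be performed by one of two registered physiotherapists". The preparation is shared: "both physiotherapists will have completed two comprehensive training sessions together". The written protocol given to them covers "application of both the rigid and elastic taping techniques, prescription of the lower limb muscle training exercises, and recording of treatment".
- **Blinding (Study design):** "it will not be possible to blind the treating physiotherapist or the participants".
- **Sequence (Randomisation):** "a computer-generated table of random numbers (in three blocks) will be used for the randomisation sequence". No stratification factor is named.
- **Concealment (Randomisation):** "An individual not otherwise involved in the study will place the randomisation sequence in a series of consecutively numbered opaque envelopes". The section also says: "Allocation will be concealed from the outcome assessor for the duration of the trial".
- **Disclosure (Recruitment of participants):** the treating physiotherapist tells the participant her group once the baseline measurements are finished.
- **Model (Planned statistical analysis):** a repeated-measures analysis of variance with group and test session as factors. For every procedure, "age, weight and height will be included as covariates". Physiotherapist does not appear.

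**The concern.** The physiotherapist gives the advice, applies the tape in two arms, teaches the exercises, chooses their starting difficulty from a judged stability rating and telephones every week. Participants know their arm, and pain, function and global effect are all self-reported. Differences in manner, expectation or skill between the two physiotherapists could therefore move the outcomes.

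The covariate list is stated for all procedures. It covers age and body size but leaves out the one delivery factor that the protocol itself identifies. With 15 participants per arm, the physiotherapist mix can differ noticeably between arms by chance. As written, the model cannot remove the resulting shift from an arm contrast, and any operator variance stays in the residual.

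**Working it through.** The protocol gives no figure for an operator effect, so there is nothing of its own to reproduce on this point. The check asks how large the consequence could be.

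**Inputs from the protocol (Sample size considerations):** 15 recruited per group, 10 per group needed, target difference 20 mm on the pain VAS, SD 12.7 mm, alpha 0.05.

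**Assumptions:**
- each participant goes to either physiotherapist with probability p = 0.5, independently of arm;
- the mean VAS difference between the two physiotherapists' participants is d = 5 to 10 mm, the same in every arm;
- the 12.7 mm SD does not already contain that difference;
- the test is two-sided.

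**1. Spread of operator share between two arms.**
SD = √(2·p·(1−p)/n) = √(2 × 0.5 × 0.5 / 15) = 0.18.

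**2. Chance of a visible imbalance.** The number treated by one physiotherapist is binomial(15, p) in each arm. Twenty points is 3 of 15 participants; 33 points is 5 of 15.

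| Imbalance of at least | A given pair, 50:50 | Some pair of three, 50:50 | Some pair of three, 70:30 |
|---|---|---|---|
| 20 points | 36% | 63% | 58% |
| 33 points | 10% | 22% | 17% |

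**3. Shift in an arm contrast.** The shift is d times the difference in operator share, and its expectation is zero. Its SD is:
- d = 5 mm: 5 × 0.183 = 0.9 mm;
- d = 10 mm: 10 × 0.183 = 1.8 mm.

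**4. Compare with the sampling error already present.**
SE = 12.7 × √(2/15) = 4.6 mm.
With the operator variance added, √(4.64² + 0.91²) = 4.7 mm and √(4.64² + 1.83²) = 5.0 mm.

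**5. Effect on power.** At p = 0.5 the total SD is √(12.7² + d²/4), which is 12.9 mm for d = 5 and 13.6 mm for d = 10. Two-sample t-test, difference 20 mm:

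| Operator effect | Power, n = 10 per group | Power, n = 15 per group |
|---|---|---|
| none | 0.91 | 0.99 |
| 5 mm | 0.90 | 0.98 |
| 10 mm | 0.87 | 0.97 |

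**The case against.** The strongest defence is that operator is not tied to arm. Both physiotherapists train together and work from one written protocol that covers every treatment. Starting difficulty follows a stated rule, and foot mobility is measured before and after each taping to keep application consistent. An unstratified factor that is balanced in expectation is ordinary random error, and many sound trials leave such factors out. The 10 mm operator effect is assumed and is half the target difference, and the 63% is for the worst of three pairs. All of this stands, and it is why the point concerns precision. It does not explain why the stated covariates leave out a known delivery factor that costs one degree of freedom.

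A reader might go further and infer that the blocks are of fixed size, that late allocations are therefore predictable to the physiotherapists, and that selection bias follows. The article does not support this. It mentions three blocks without giving a size or saying whether the size is constant. It gives the physiotherapists no role in screening. Eligibility, consent and baseline measurement come before disclosure, and an independent person prepares sealed, numbered, opaque envelopes. The sentence about the outcome assessor describes blinding during the trial and does not say that others could foresee the allocation. Block size and who is kept unaware of the sequence are details that an article may leave to the full protocol.

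**Conclusion.** The point holds as a modest weakness of design and analysis. Two unblinded physiotherapists deliver the treatment, the described sequence is not stratified by physiotherapist, and the stated model has no term for them. For an assumed operator effect of 5 to 10 mm, the omission adds a chance component with SD of about 0.9 to 1.8 mm to an arm contrast, and lowers VAS power at 10 per group by about 1 to 4 percentage points.

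Systematic bias might be inferred, but it would require the physiotherapist to be chosen according to the arm. The article does not say how participants are assigned to a physiotherapist. Because the treating physiotherapist announces the allocation, that person appears to be settled beforehand. The sizes rest on the assumed caseload split and operator effect, neither of which the protocol gives.

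**What to change.** 1. Add treating physiotherapist as a fixed factor (main effect) to the repeated-measures models in Planned statistical analysis, alongside the stated covariates.
2. State that the physiotherapist is assigned before the envelope is opened, so that the choice cannot depend on the arm.
3. Where scheduling allows, stratify the sequence by physiotherapist, with randomly varying block sizes within each stratum.

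**Cost:** one degree of freedom in the model, a second set of envelopes from the same independent person, and possibly slightly unequal arms. If stratification is not practical, the first two steps keep most of the benefit: the factor removes the effect of chance imbalance from the contrast, and assigning the physiotherapist first keeps that imbalance a matter of chance.

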#### Lower limb muscle training alone

Participants in this group will receive advice and education and will be prescribed an exercise program to perform at home. At the completion of the baseline outcome measurements, the physiotherapist will provide a standardised information sheet with advice and education regarding ERLP, as well as load management. Participants will be advised not to start any new activities or treatments for the duration of the study, encouraged to continue to wear current footwear (including orthotic use) and participate in activities that do not provoke symptoms and to avoid activities that aggravate symptoms either during or following the activity; as treatment progresses, this may include a return to participation in activities that previously aggravated symptoms.

At the end of week 1, the participant will attend a thirty minute physiotherapy session where advice and education information will be reviewed with the patient and training in the exercise program will commence. The exercise program will include two exercises: (i) the plantar intrinsic foot muscle exercise [21] (Figure 2), and (ii) hip abductor and external rotator muscle exercise (Figure 3). The difficulty of both exercises can be increased from non-weightbearing, to double-limb weightbearing and then single-limb weightbearing (Figures 2 and 3). A rating scale to assess the intrinsic foot muscles [21], based on unsteadiness of navicular height during single-limb stance, will be used to decide the difficulty of the exercises prescribed at the first session: non-weightbearing exercises will be prescribed for a rating of poor stability; double limb weightbearing exercises will be prescribed for a rating of fair stability, and single-limb weightbearing will prescribed for a rating of good stability. Participants will be instructed how to perform the exercises at each level of difficulty, and will be encouraged to increase the difficulty of the exercises when full repetitions are achieved (3 minutes for intrinsic foot muscles, 3 × 20 second holds for gluteal muscles). Participants will be instructed to perform the exercises daily and record the exercises they completed and their difficulty level in a training diary for the duration of week 2 of the trial. At the end of week 2, the participant will attend a thirty minute physiotherapy session to reinforce advice and education, review the exercise program and progress exercises as able. Participants will be instructed to perform the exercises daily and record the exercises they completed and their difficulty level in a training diary for a further 4 weeks. To check exercise progression and encourage compliance, the treating physiotherapist will contact participants weekly by telephone. At conclusion of the 6 week intervention, participants will be encouraged to continue prescribed exercises and load management strategies and this self management will be recorded in follow-up questionnaires at 12, 18, 24 and 30 weeks.

**Figure 2 Fig2:**
[figure not shown]
**Plantar intrinsic foot muscle training.** Plantar intrinsic foot muscle training will be performed as described by Mulligan et al. [21]. Active intrinsic foot muscle exercises may be commenced in a non-weight bearing sitting position **(A)**. The patient is instructed to increase the medial longitudinal arch by gently supinating the foot and approximating the head of the first metatarsal towards the heel, without flexing the toes. This position should be held for 5 seconds and then slowly released back to a relaxed state. Patients should aim to perform up to 3 minutes of this exercise daily. Exercises can then be progressed to functional weight bearing positions, for example double-limb stance **(B)** and single-limb stance **(C)**. For further progression, a small knee bend **(D)** and/or heel raise **(E)** can be added to these functional positions.

**Figure 3 Fig3:**
[figure not shown]
**Hip abductor and external rotator muscle training.** For the non-weight bearing and weight bearing exercises, the patient will perform a 20 second hold and aim to perform 3 repetitions, daily. The non-weight bearing exercise **(A)** will be performed in side-lying with the treatment limb uppermost and both limb flexed to 45° at the hip and 90° at the knee. Ideally the patient’s back and plantar surface of the foot are placed against a wall for control of position and movement. The patient raises the top limb off the other, such that the hip is in ~30° abduction/external rotation before returning to the starting position. The weight bearing exercise **(B)** is performed with the patient standing side-on to a wall with body rotated slightly to face into the wall. The leg closest to the wall is flexed at the knee so that the foot is off the ground, and the hip is in neutral flexion/extension. The foot of the leg closest to the wall is tucked behind the knee of the outer leg. The standing leg knee should be bent slightly. The patient is instructed to squeeze the bottom together and hold this throughout the movement, then turn the knee of the standing leg out without moving the foot or pelvis. The bent leg is held against the wall for balance only.

#### Combined rigid anti-pronation taping and lower limb muscle training

Participants will receive advice and education, be prescribed an exercise program and wear rigid ALD taping [25] (Figure 4). At the completion of the baseline outcome measurements, the physiotherapist will provide a standardised information sheet, as described above. Following this, ALD taping will be applied using a rigid sports tape (38 mm zinc oxide adhesive, Leukosport BDF™) and the appropriate skin checks made and warnings given. Participants will be re-taped half way through week 1; no advice or education regarding the exercises will occur during this session. Participants will be instructed to remove the tape and any tape residue the night prior to attending the testing session. At the end of week 1, the participant will attend a thirty minute physiotherapy session where advice and education will be reinforced, the ALD tape re-applied and training in the exercise program commenced. The exercise program will include the same two exercises as described above: (i) intrinsic foot muscle exercise, and (ii) hip abductor and external rotator muscle exercise. Participants will be instructed to perform the exercises daily and record their performances in a training diary for the duration of week 2 of the trial. Participants will be re-taped half way through week 2; no advice or education regarding the exercises will occur during this session. Participants will be instructed to remove the tape and any tape residue the night prior to attending the testing session. At the end of week 2, the participant will attend a thirty minute physiotherapy session to reinforce advice and education, review the exercise program and progress exercises as able. Participants will be instructed to perform the exercises daily and record in a training diary for a further 4 weeks. To check progress and encourage compliance, the treating physiotherapist will contact participants weekly by telephone. No taping will be applied during these final 4 weeks of the intervention.

**Figure 4 Fig4:**
[figure not shown]
**Rigid anti-pronation taping technique (ALD).** The ALD technique will be applied following guidelines previously described [25]. The ALD comprises of a low-Dye technique **(A)** with the addition of three reverse-6 techniques **(B)** and two calcaneal sling techniques **(C)** that are anchored to the lower third of the leg. The technique is completed with circumferential lock off strips from the proximal anchor to just above the malleoli **(D)**.

#### Elastic anti-pronation taping and lower limb muscle training

Participants will receive advice and education, be prescribed an exercise program and wear an elastic anti-pronation taping [26] (Figure 5). At the completion of the baseline outcome measurements, the physiotherapist will provide advice and education regarding the condition and load management. Following this, elastic anti-pronation taping will be applied using an elastic tape (50 mm & 75 mm, Beige Dynamic Tape™) and the appropriate skin checks made and warnings given. Participants will be re-taped half way through week 1; no advice or education regarding the exercises will occur during this session. Participants will be instructed to remove the tape and any tape residue the night prior to attending the testing session. At the end of week 1, the participant will attend a thirty minute physiotherapy session where advice and education will be reinforced, the elastic tape re-applied and training in the exercise program will commence. The exercise program will include the same two exercises as described above: (i) intrinsic foot muscle exercise, and (ii) hip abductor and external rotator muscle exercise. Participants will be instructed to perform the exercises daily and record their performances in a training diary for the duration of week 2 of the trial. Participants will be re-taped half way through week 2; no advice or education regarding the exercises will occur during this session. Participants will be instructed to remove the tape and any tape residue the night prior to attending the testing session. At the end of week 2, the participant will attend a thirty minute physiotherapy session to reinforce advice and education, review the exercise program and progress exercises as able. Participants will be instructed to perform the exercises daily and record in a training diary for a further 4 weeks. To check progress and encourage compliance, the treating physiotherapist will contact participants weekly by telephone. No tape will be applied during these final 4 weeks of the intervention.

**Figure 5 Fig5:**
[figure not shown]
**Elastic anti-pronation taping technique.** The elastic anti-pronation taping technique will be applied following Dynamic Tape™ guidelines for the plantar fascia and anti-pronation techniques [26]. For each technique a double layer of 50 mm Dynamic Tape™ will be used. The plantar fascia technique **(A)** is applied by cutting out a small wedge from one end of the double layered tape to allow it to conform to the proximal phalanx of the first toe. With the foot and ankle in full plantarflexion, inversion, adduction and flexion of the first toe, the tape is applied from the plantar surface of the first toe, along the medial plantar aspect of the foot, onto the medial aspect of the calcaneus, around the calcaneus to cross the lateral aspect obliquely, continuing under the plantar aspect of the foot to emerge under the navicular and finally lifting the navicular to anchor the tape on the dorsum of the foot. The anti-pronation technique **(B)** is then applied with the foot and ankle in full dorsiflexion, inversion, and adduction. The double layered tape is applied from the plantar surface of the foot between the first and second metatarsals, courses over the dorsum of the foot from medial to lateral, under the plantar aspect of the foot on a diagonal course to the navicular, lifting the navicular and coursing across the anterior talocural joint to anchor on the lateral aspect of the mid-shin region. The anti-pronation technique is then repeated with one layer of 75 mm Dynamic Tape™ **(C)**.

